### Recruitment

This multi-center, randomized, sham-controlled, patient and assessor blinded trial will be conducted in the Shanghai Yueyang Hospital of Integrated Traditional Chinese and Western Medicine, Shanghai Municipal Hospital of Traditional Chinese Medicine, Shanghai Chest Hospital, and LongHua Hospital Shanghai University of Traditional Chinese Medicine. Participants of the study will be recruited through the outpatient clinic or inpatient, hospital-based Wechat advertising, and posters in the hospital. Any interested patients will be screened by telephone or on site and consented for the study. After being informed of the details of this RCT, participants will be asked to provide signed informed consent, and deliver it to an independent research assistant. Patients will be randomly divided into two groups: the acupuncture group (*n* = 160) and the sham acupuncture group (*n* = 160). All participants will undergo 6-week treatment with acupuncture (or sham acupuncture) and a series of assessments of CRF, free of charge. Timing of treatment assessments and data collection are as follows in Table 1.

**Table 1 Tab1:** Timing of treatment assessments and data collection

	Study period					
	Enrollment	Baseline	Treatment phase		Follow-up phase	
Timepoint	-1 week	0 weeks	3 weeks	6 weeks	4 weeks	12 weeks
Enrollment						
Eligibility screen	X					
Informed consent	X					
Medical history	X					
Allocation		X				
Interventions						
Acupuncture		X	X	X		
Sham acupuncture		X	X	X		
Assessments						
Primary outcome						
BFI-C		X	X	X	X	X
Secondary outcomes						
EORTC QLQ-C30		X		X		
HAMD		X		X		
Others						
Adverse events		X	X	X		
Patients’ satisfaction				X		
Success of blinding				X		

*BFI-C* Brief Fatigue Inventory-Chinese, *EORTC QLQ-C30* European Organization for Research and Treatment of Cancer Quality of LifeQuestionnaire, *HAMD* Hamilton Rating Scale for Depression

#### Inclusion criteria

Participants with the following conditions will be included:
Participants in line with interpretation of Chinese lung cancer treatment guidelines (2015 edition) for the diagnosis of lung cancer [14]Imaging evidence that supports a diagnosis of lung adenocarcinomaResection surgery performed within the last 3–6 months but no chemotherapyMeet the diagnostic criteria for CRF [15] and BFI-C score > 4Age 18–75 yearsKarnofsky Performance Status (KPS) score > 80 [16]Able to understand the nature of the study and willing to give informed consentCapable of providing responses during outcome measurement

#### Exclusion criteria

Participants with the following conditions will be excluded:
Comorbidities such as serious heart, kidney, or liver diseaseSevere mental disorder such as cognitive impairmentOther physiological or pathological causes of fatigue such as chronic fatigue syndrome (CFS)Acupuncture received within the past 6 monthsPregnancy or currently lactating

### Randomization and allocation concealment

Stratified block randomization will be used in this experiment. An independent statistician will generate the randomization sequence using SPSS 23.0. The participants who meet the criteria will be randomly assigned to one of the two groups in 1:1 ratio by computer-generated random sequences after completion of the baseline assessment. Participants will be randomized in blocks of 4–8 at each center. The randomization will be concealed by using opaque envelopes. The treatment allocation codes will not be revealed until the participants have finished all baseline assessments and before the first acupuncture treatment. In order to minimize breaks in coding, the principal investigator (PI) who designed the trial and research personnel who perform the outcome assessments will be blinded to the treatment assignment. Only the acupuncturists will know which participants belong to which groups.

### Blinding

Participants will be informed that they will be randomly assigned to either acupuncture treatment or acupuncture-like simulation treatment. Participants will be asked to wear an eye-patch when they receive treatment: the two groups will receive identical treatment except no skin penetration will be involved in the sham acupuncture group. Therefore, participants and other researchers (the PI, data analysts, outcome assessors, and statistician) will be blinded to the group allocation. All researchers will be trained before the trial begins, to ensure the successful implementation of the blinding method.

### Intervention protocol

The acupuncture treatment will be conducted after all participants have given informed consent. All patients will receive 12 treatments, either acupuncture or sham acupuncture twice per week for 6 weeks. In each treatment session, every patient will be placed in a separate space and asked to wear an eye-patch. Each procedure will last 30 min and will be performed by a trained acupuncturist who will be a registered practitioner with more than 3 years of experience in clinical practice. The acupuncturist will confirm that the participant has undergone the assigned procedure. To improve patients’ compliance, all patients will receive the intervention and assessments by telephone reservation.

The acupuncture procedure will be performed following the Guidance of Clinical Practice of Acupuncture [17]. Before treatment, the patients’ skin will be sterilized using alcohol wipes, then the experienced acupuncturists will begin the treatment. In the treatment group, acupuncture needles will be standard stainless steel, sterile, and disposable (0.25 × 40 mm and 0.30 × 40 mm in length; Jia Jian, China). The Streitberger placebo-needle will be used at the same acupoints in the control group. The methods and acupoints for acupuncture treatment are shown in Table 2. Any concomitant care or intervention that has the effect of supplementing *Qi* (traditional Chinese medicine term) is not allowed to be used during the treatment and follow-up period, including using some special herbs and exercising Qi-Gong et al.

**Table 2 Tab2:** Details of intervention

	Intervention group	Control group
Acupoints	GV20, GV29, CV12, CV6, CV4, LI4, LR3, SP6, ST36	GV20, GV29, CV12, CV6, CV4, LI4, LR3, SP6, ST36
Depth of insertion	GV20, GV29, LI4, LR3 10 mm	No insertion
	CV12, SP6, CV6, CV4, ST36 30 mm	
Needle type	Steel needle (Wuxi Jiajian Medical Co. Ltd. Wuxi, China)	Blunt-tip needle (Streitberger placebo-needle)
Needle sensation	With de-qi sensation	Without de-qi sensation
Electric stimulation	Needle on bilateral ST36 connected to SDZ-III Electronic Acupuncture Treatment Instrument (Hwato, China). with electric pulse at a frequency of 2.5 Hz and an intensity of 45 mA	Needle on bilateral ST36 connected to SDZ-III Electronic Acupuncture Treatment Instrument (Hwato, China). without electric pulse
Frequency and duration	Twice per week for 6 weeks	Twice per week for 6 weeks

### The acupuncture group

The acupuncture group will receive real acupuncture treatment for 6 weeks. According to our previous experience, *Baihui* (GV20), *Yintang* (GV29), *Zhongwan* (CV12), *Qihai* (CV6), *Guanyuan* (CV4), bilateral *Hegu* (LI4), bilateral *Taichong* (LR3), bilateral *Sanyinjiao* (SP6), and bilateral *Zusanli* (ST36) will be used as the acupoints for treatment. Patients will be treated in the supine position at GV20, CV12, CV6, CV4, and LI4 (with the needle tip pointing towards the ground), at CV29 and LR3 (with the needle tip pointing towards the feet), and at SP6 and ST36 (with the needle tip pointing towards the limb extremities). All the acupoints will be punctured perpendicularly to the respective depth of 10–30 mm, manipulating manually (including lifting, thrusting, and rotating) until the patient reports needling sensations (*Deqi* sensation). The needles on the bilateral *Zusanli* (ST36) will be connected to an SDZ-III Electronic Acupuncture Treatment Instrument (Hwato, China), using continuous wave type stimulation, with a frequency of 2 Hz, and intensity of 2~3 mA. Needles will be retained for 30 min.

### The control group

The control group will undergo treatment with special sham acupuncture. We will use a non-invasive placebo control, the Streitberger placebo-needle. Acupoints will be the same as in the acupuncture group but without insertion of the needle. Similarly, the electroacupuncture apparatus (SDZ-III Electronic Acupuncture Treatment Instrument) will be set beside the patients and connected to the bilateral *Zusanli* (ST36), without an electrical pulse. This set up will remain in place for the next 30 min.

### Outcome measures

We will assess the primary outcome at baseline, week 3, post treatment (week 6), and at follow up at the 4th and 12th weeks after the end of treatment. Secondary outcomes will be assessed at baseline and week 6.

### Primary outcome

#### Brief Fatigue Inventory-Chinese version (BFI-C)

The change in BFI-C scores will be used to evaluate the degree and impact of fatigue. The Brief Fatigue Inventory scale is designed by Mendoza [18] and translated by Wang [19], and it comprises two parts, (the first part consists of 1–3 items, the second part consists of 4–9 items), and questionnaire items 1–3 are used to assess the individual’s overall fatigue level over the past 24 h. The items 4–9 are designed to evaluate the effects of fatigue on general activities, emotions, walking ability, normal work (including work and housework), relationship with others, and enjoyment of life. The scale uses the 10-point scoring method, whereby 0 points indicates no fatigue and 10 points the most severe fatigue. A higher score indicates more severe fatigue. According to the average score, it can be divided into four grades, that is no fatigue (score 0), mild fatigue (score 1–3), moderate fatigue (score 4–6), and severe fatigue (score 7–10). The BFI scale has been validated in patients with different types of cancer all over the world [19–21]; the structural validity is 0.81–0.92, and the Cronbach’s coefficient of the total scale is 0.96. The Chinese version of the BFI has been proven to have good reliability and validity [19]. The mean of the change in score on the BFI-C at week 6 will be analyzed as the primary outcome.

### Secondary outcomes

#### European Organization for Research and Treatment of Cancer Quality of Life Questionnaire (EORTC QLQ-C30)

The EORTC QLQ-30 is a core scale developed by the European Organization for Research and Treatment (EO RTC) for the determination of quality of life in patients with cancer [22]. It includes a total of 30 entries, which are divided into 15 domains; among these there are 5 functional domains (body, role, cognition, mood, and social function), 3 symptom domains (fatigue, pain, and nausea and vomiting), 1 overall health status/quality of life area and 6 single entries (each as a domain). The higher the score for the functional domains and overall health status, the better the functional status and quality of life. The higher the score for the symptom domains, the worse the quality of life. The mean of any change in score at week 6 will be analyzed.

### Hamilton Rating Scale for Depression (HAMD)

The HAMD developed in 1960 [23, 24] is the questionnaire used to describe the severity of cognitive and bodily symptoms of depressive disorders. Each item is rated on 3-point or 5-point scales. According to the total score, depression can be divided into four grades: normal (total score < 7); patient may have depression (total score 7–17); depression (total score 17–24); and severe depression (total score > 24). The higher the total score, the more significant the tendency toward depression. The mean of any change in score at week 6 will be analyzed.

### Safety assessment

Any adverse events occurring during the trial will be recorded by the patients and physicians. Any discomfort, symptoms, or other diseases will be assessed. All details of adverse events will be reported in the case report form. The researcher will interview participants and write an adverse event report after treatment. The Data and Safety Monitoring Board and Ethic Review Board will assess any correlation between the adverse event and the intervention, and make the final decision as to whether to continue the study or not. We will analyze the influence of all events at the end of the trial.

### Credibility of Treatment Rating Scale (CTRS)

The CTRS is a scale for assessing the credibility of the acupuncture treatments. It consists of four items and is used to assess the participants as “perceived logic of the treatment,” “confidence in recommending the treatment to their friends who have similar complaints,” “confidence in the treatment to alleviate their complaint,” and “likelihood that the treatment would alleviate their other complaints.” A lower score indicates greater confidence in the received treatment [25, 26].

### Assessment of blinding 

After the final treatment session, the success of the blinding method will be tested by asking the participants the following question “When you volunteered for the study, you were informed that you had an equal chance of receiving traditional acupuncture or acupuncture-like simulation treatment. Our study is finished now, which style acupuncture do you think you are received?” The participants will be provided with three choices of response to this question: acupuncture, acupuncture-like simulation, or uncertain. If participants do not chose “uncertain”, we will ask the reason why they have made that assumption [27].

### Quality control

The Clinical Research Center of Drugs of Shanghai University of Traditional Chinese Medicine Data Monitoring Team will be responsible for controlling bias and identifying problems in the project. In order to guarantee the quality of this study, every acupuncturist in this trial will be a registered practitioner with 3–5 years of clinical experience in the practice of acupuncture. Meanwhile, a qualified clinical trial expert will monitor every trial center, and regular board meetings will be held to ensure the quality of the study process.

### Monitoring

According to recommendation of the National Institutes of Health (NIH), a Data and Safety Monitoring Board (DSMB) will be formed to monitor the trial progress and review the safety and quality of the data [28]. The committee consists of three members, including a senior acupuncturist, an oncologist, and a statistician (Additional file 2). The DSMB is independent of the proposed trial and all members will have to declare any conflict of interest in the trial. Regular meetings will be held during the trial, to ensure the data are collected scientifically and ethically. Moreover, the DSMB can ensure participants are not exposed to unnecessary risks, and has the right to unblind the study if serious adverse events related to the intervention occur. The DSMB will provide data monitoring with access to any interim results and will make the final decision to terminate the trial if necessary. It also will identify problems in the project, if any, make decisions on changing the details of this protocol, apply for approval from the Ethics Review Board by written application, and announce the persons conducting the trial by written notice after approval is received from the ethics committee. Besides this, a qualified clinical trial expert will be invited to monitor this study, and the PI will take full responsibility and make any final decisions.

### Clinical trial registration

This RCT was registered in the Chinese Clinical Trial Registry (ChiCTR1900022831) on 27 April 2019. The URL is http://www.chictr.org.cn/showproj.aspx?proj=37823.

### Data management

The participant will be interviewed at each time point, and further cancer care advice will be given at the interview. This procedure will promote retention of participants and completion of follow-up assessments. All the original data will be collected by blinded assessors and double-entered into the electronic data capture system (EDC). The system will be tested before it is officially launched to ensure that it meets the trial requirements. The original data recorded in case report forms will be entered into the EDC within 1 week after the participants have finished all the treatments and follow-up assessments. Codes and initials will be used in the case report forms, instead of the participant’s information, to protect the participant’s privacy. If the data are found to be uncertain, the data supervisor will notify the researcher to respond with a data question form. If necessary, the statistician will send a data question form to the researcher and the researcher’s answer will be entered on the form. The inspector will then return the question form to the statistician.

### Statistical analysis

Statistical analysis of data will be carried out using SPSS 23.0 software. We will use multiple imputation to address any missing data. An independent statistician, who will be blinded to group allocation, will analyze all data, including those from any participants who drop out during the trial, using the intention-to-treat (ITT) method. Baseline demographics will be analyzed descriptively. Changes in BFI-C will be compared between the two groups as the primary analysis, using repeated measures analysis of variance (ANOVA (general linear model)). For the secondary outcomes, scores on the QLQ-C30, HAMD, and CTRS will be compared between the two groups using Student’s *t* test or the Wilcoxon rank-sum test. All reported *P* values will be two-sided, and a *P* value of less than 0.05 will be considered statistically significant. The mean difference and confidence intervals at the 95% level will also be calculated using SPSS.

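### The planned BFI-C ANOVA and the t-or-Wilcoxon option need not give a P value that matches the week-6 mean difference, and neither adjusts for baseline as a covariate or for centre

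*Protocol article*

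**What the plan says.** All references are to the protocol article.

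- **Primary outcome** (Brief Fatigue Inventory-Chinese version section): "The mean of the change in score on the BFI-C at week 6 will be analyzed as the primary outcome".
- **Primary test** (Statistical analysis): "Changes in BFI-C will be compared between the two groups as the primary analysis, using repeated measures analysis of variance (ANOVA (general linear model"). Table 1 schedules BFI-C at five times: baseline, weeks 3 and 6, and 4 and 12 weeks after treatment ends. The text does not say whether the group effect or the group-by-time effect decides.
- **Secondary tests** (Statistical analysis): QLQ-C30, HAMD and CTRS scores "will be compared between the two groups using Student’s" t "test or the Wilcoxon rank-sum test". No rule for choosing between the two is given. The sections on the QLQ-C30 and the HAMD make the week-6 change the quantity analysed.
- **Estimates** (Statistical analysis): "The mean difference and confidence intervals at the 95% level will also be calculated using SPSS".
- **Missing data** (Statistical analysis): "We will use multiple imputation to address any missing data". The Sample size section allows for 20% dropout.
- **Stratification** (Randomization and allocation concealment): blocks are formed within each centre. No analysis named in the article includes centre.

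**The concern.** A trial with one primary endpoint at one time point needs its P value, estimate and confidence interval to concern the same quantity. Here they need not.

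- **BFI-C.** The group effect of a repeated-measures ANOVA averages over visits, including two after treatment has ended. The group-by-time effect asks whether the between-group difference varies over visits. Either can be significant when the week-6 difference is not, or the reverse.
- **QLQ-C30 and HAMD.** A rank-sum P value would stand beside the confidence interval of a mean difference, which is a different quantity. The rank-sum test also gives no estimate with a standard error that Rubin's rules could combine over imputed data sets. Naming two tests for the same outcomes leaves the choice open until the data are seen.
- **Precision.** Baseline scores are collected and randomisation is stratified by centre, yet the named comparisons use baseline only by subtraction and do not use centre.

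At stake are a clear answer on the primary outcome, agreement between P values and intervals, and precision that costs nothing to obtain.

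**Working it through.** **1. The plan's own figure.** Inputs from Sample size: difference 0.35, SDs 1.03 and 1.00, two-sided 0.05, 80% power.

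- Common SD = √((1.03² + 1.00²)/2) = 1.015.
- n = 2(1.960 + 0.842)² × 1.015² / 0.35² = 132.05, rounded up to 133 per group. The figure reproduces. The unequal-variance t test has power 0.79996 at 133.

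The trial was therefore sized for a single difference in mean change, not for an ANOVA F test.

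**2. What each BFI-C effect estimates.** Assume 160 per arm, complete data, SD 1.015 and correlation 0.6 between the changes at the four post-baseline visits. The article gives no such correlation.

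- SE of the week-6 difference = 1.015 × √(2/160) = 0.1135.
- SD of a patient's average over four visits = 1.015 × √((1 + 3 × 0.6)/4) = 0.849. SE of the group effect = 0.849 × √(2/160) = 0.0950.
- Power ≈ Φ(difference/SE − 1.96) for these two. For the interaction it comes from the noncentral F with 3 and 954 df and noncentrality 80 × (sum of squared deviations of the visit differences from their mean)/(1.015² × 0.4).

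| Assumed true differences (wk 3, wk 6, +4 wk, +12 wk) | Group effect estimates | Power: week-6 contrast | Power: group F | Power: group × time F |
|---|---|---|---|---|
| 0.175, 0.35, 0.35, 0.35 | 0.306 | 0.87 | 0.90 | 0.39 |
| 0.35 at all four | 0.35 | 0.87 | 0.96 | 0.05 |
| 0.175, 0.35, 0.175, 0 | 0.175 | 0.87 | 0.45 | 0.83 |

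The week-6 difference is 0.35 in every row, but the ANOVA result depends on the other visits.

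**3. The first profile with dropout and imputation.** A simulation used 160 per arm, completely random monotone dropout of 10% at week 3 and 20% from week 6, 20 imputations and 600 runs. Power was 0.81 for the Rubin-pooled week-6 difference, 0.86 for the pooled group F and 0.32 for the pooled group-by-time F (Monte Carlo standard errors 0.014 to 0.019).

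**4. Secondary tests.** If the smaller of the t and rank-sum P values were always reported at 133 per arm, simulated type I error was about 5.6% to 7.9%, lowest for normal and highest for skewed data. If the test were chosen by a normality check in each arm, it was 0.049 to 0.053.

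**5. Baseline adjustment.** Assume equal variance σ² at baseline and week 6, with correlation ρ.

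- Change score: variance 2σ²(1 − ρ).
- ANCOVA: variance σ²(1 − ρ²).
- Ratio: (1 + ρ)/2.

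| Assumed ρ | Variance ratio | Variance reduction | CI width ratio (square root) |
|---|---|---|---|
| 0.3 | 0.65 | 35% | 0.81 |
| 0.5 | 0.75 | 25% | 0.87 |
| 0.7 | 0.85 | 15% | 0.92 |

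Any gain from adjusting for centre is not included, because the article gives nothing from which to compute it.

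**The case against.** The strongest reply is that the plan can be carried out validly as written, and that the rest is detail for an analysis plan. Several parts of this stand.

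- **Pooling.** A reader might infer that multiple imputation cannot be combined with these tests. That is not so. The t test yields a difference and a standard error. With two arms the ANOVA group effect has one degree of freedom and is equivalent to such a difference. The promised mean difference can be pooled directly, and F tests can be combined by the D2 rule. In 1,500 null simulations type I error was 0.052 for the pooled week-6 difference, 0.052 for the pooled group F and 0.045 for the pooled group-by-time F. Only the rank-sum test lacks a direct estimate for Rubin's rules.
- **Inflated error.** A reader might go further and expect P values that ignore imputation uncertainty. Using the within-imputation variance alone would give 2(1 − Φ(1.96√0.9)) = 6.3% or 2(1 − Φ(1.96√0.8)) = 8.0% for 10% or 20% missing information. The article says multiple imputation, and nothing in it points to a single imputed set or averaged P values. The number of imputations, the imputation model and the pooling rule may properly sit in the analysis plan.
- **Baseline.** It would be wrong to say that baseline is ignored, because change scores use it. Change score and ANCOVA are both unbiased under randomisation, so the argument is one of precision.
- **Test choice.** Choosing by distribution is the customary reading and kept the error near 5%. The 5.6% to 7.9% is a worst case, for secondary outcomes only.

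The reply does not remove the mismatch of targets. The article itself fixes a week-6 endpoint, an all-visit test and a mean difference with CI. These differ whether or not data are missing.

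**Conclusion.** The point holds as a mismatch between endpoint, test and estimate, together with an avoidable loss of precision. It is not a claim that the imputation is invalid or that the plan inflates the type I error.

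- **Primary outcome.** With the same week-6 difference of 0.35, power was 0.81, 0.86 or 0.32 depending on which effect decides. This rests on the assumed correlation of 0.6, the assumed profile over visits, random dropout and an ANOVA of the four post-baseline changes. The figures would move under other assumptions, and also if baseline were entered as a fifth level of time. That the three effects are different quantities does not depend on them.
- **Secondary outcomes.** A rank-sum P value does not correspond to the promised interval.
- **Precision.** ANCOVA cuts the variance of the change-score comparison by 35%, 25% or 15% for assumed correlations of 0.3, 0.5 or 0.7, with equal variances. For BFI-C the ratio is approximate, because the entry threshold of a score above 4 may narrow the spread at baseline.

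The plan should be changed before the data are unblinded. The fault is moderate, because a valid route exists but the text does not lead to it.

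**What to change.** 1. **BFI-C.** Take the primary P value, difference and 95% CI from one source: the week-6 between-group contrast of an ANCOVA or a linear mixed model, adjusted for baseline score and centre. Pool the contrast and its standard error over imputations by Rubin's rules, or use the likelihood-based mixed model without imputation. Report the other visits and any group-by-time effect as supportive.
2. **QLQ-C30 and HAMD.** Replace the two-test option with a prespecified ANCOVA of the week-6 score on group, baseline and centre, pooled in the same way. Keep the rank-sum test as a sensitivity analysis only.
3. **CTRS.** Table 1 shows no baseline for it, so naming one test in advance is enough.

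The cost is a few sentences in the analysis plan and a different model in the software. No extra data are needed, since baseline scores and centre are already recorded.

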## Methods/design

### Study design

We propose a multi-center, randomized, sham-controlled, patient and assessor blinded trial. The trial commence in four centers after ethical approval has been obtained from the Institutional Review Board. The clinical trial is designed and reported following the Consolidated Standards of Reporting Trials [11] and Standards for Reporting Interventions in Clinical Trials of Acupuncture guidelines [12]. Eligible patients will be randomly divided into the acupuncture group and the sham acupuncture group in a 1:1 allocation ratio. All participants will provide signed informed consent before proceeding with the trial. The flow chart of the study process is shown in Fig. 1.

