### Sample size

The sample size calculation was based on change in BFI-C scores. According to previous studies [13], we assume the change is − 2.35 in the acupuncture group and − 2.0 in the sham-acupuncture group; therefore, the mean difference between two group is 0.35 with standard deviations of 1.03 and 1.00, and a sample size of 133 per group will provide 80% power to reject the null hypothesis with a significance level of 0.05, using a two-sided, two-sample, unequal-variance *t* test. Allowing for a dropout rate of 20%, a total of 320 participants should be recruited for this trial.

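### The named analyses of BFI-C, QLQ-C30 and HAMD include neither the baseline score nor the stratifying centre; this loses precision but does not bias the estimate

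*Protocol article*

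**What the plan says.** All references are to the protocol article.

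- **Primary analysis** (Statistical analysis): "Changes in BFI-C will be compared between the two groups as the primary analysis", by repeated measures ANOVA within a general linear model. No baseline covariate and no centre term is named. The Primary outcome section fixes week 6 as the time point.
- **Secondary analyses** (Statistical analysis): "scores on the QLQ-C30, HAMD, and CTRS will be compared between the two groups using" one of two tests, either the t test or Wilcoxon's rank-sum test. The QLQ-C30 and HAMD sections say that change at week 6 is analysed.
- **Baseline data** (Table 1 and Outcome measures): BFI-C, QLQ-C30 and HAMD are all taken at baseline. CTRS does not appear in Table 1, and no baseline CTRS is described.
- **Randomization** (Randomization and allocation concealment): stratified blocks, with "Participants will be randomized in blocks of 4–8 at each center". The Recruitment section lists four centres.
- **Sample size**: the assumption is that "the mean difference between two group is 0.35 with standard deviations of 1.03 and 1.00". From this the protocol derives 133 per arm for 80% power at the 5% level, by an unequal-variance t test without covariates. The total follows from the dropout allowance: "Allowing for a dropout rate of 20%, a total of 320 participants should be recruited for this trial".

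**The concern.** The trial collects two pieces of information that its named analyses do not use.

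First, a change score fixes the coefficient of baseline at 1. The data usually support a different coefficient, and the difference shows up as extra error variance. ANCOVA estimates the coefficient instead.

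Second, blocking within centre balances the arms on centre. This reduces the true variance of the treatment difference, but an analysis without a centre term still estimates the larger, unstratified variance. Its standard errors are therefore somewhat too large and its tests somewhat conservative.

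The trial is sized at 80% power for a difference of 0.35 on a 0 to 10 scale, so precision is not plentiful. If the adjustment is not fixed before unblinding, adding it later becomes a post hoc choice.

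**Working it through.** **Inputs from the Sample size section.** Difference 0.35; SDs of change 1.03 and 1.00; two-sided 5%; 133 per arm; 20% dropout; 320 in total. Allocation is 1:1 (Study design).

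**Assumed, because the document gives no value.** Correlation r between baseline and week-6 BFI-C: 0.3 to 0.7. Ratio k = baseline SD / week-6 SD: 1, and 0.6 to 0.8. Share c of outcome variance due to centre: 0.01 to 0.10. The two-sample test on week-6 change that the protocol used for sizing stands in for the primary analysis.

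**Step 1: reproduce the plan.** Pooled SD = √[(1.03² + 1.00²)/2] = 1.015. Normal approximation: n = 2 × (1.960 + 0.842)² × 1.015² / 0.35² = 132.05, so 133 per arm. The Welch noncentral-t calculation gives 79.996% power at 133. The stated figure reproduces.

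**Step 2: completers.** 133 × 1.2 = 159.6, rounded to 160 per arm. With 20% lost, 160 × 0.8 = 128 per arm. Unadjusted Welch power at 128 is 78.5%.

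**Step 3: baseline adjustment.** With the week-6 SD as the unit:

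- Var(change) = k² + 1 − 2rk
- Var(ANCOVA) = 1 − r²
- Ratio = (1 − r²) / (k² + 1 − 2rk), which is (1 + r)/2 when k = 1

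Each planned change SD is multiplied by √ratio, and Welch power is recomputed at 128 per arm:

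| k | r = 0.3 | r = 0.5 | r = 0.7 |
|---|---|---|---|
| 1 | ratio 0.65, 92.6% | 0.75, 88.7% | 0.85, 84.6% |
| 0.8 | 0.78, 87.3% | 0.89, 82.8% | 0.98, 79.2% |
| 0.7 | 0.85, 84.6% | 0.95, 80.5% | 1.00, 78.5% |
| 0.6 | 0.91, 82.1% | 0.99, 79.0% | 0.98, 79.2% |

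A value of k below 1 is plausible, because entry requires BFI-C above 4 (Inclusion criteria), which tends to narrow the baseline spread. The gain over 78.5% runs from nothing (k = r = 0.7, where the best baseline coefficient r/k is exactly 1) to about 14 points. The ratio never exceeds 1.

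**Step 4: centre.** Residual variance is multiplied by (1 − c). At 133 per arm, adjusted Welch power is 80.4%, 82.0% and 84.0% for c = 0.01, 0.05 and 0.10, which is 0.4 to 4 points above the planned 80.0%. If centre is ignored after stratified randomization, the true two-sided type I error is 2 × [1 − Φ(1.960/√(1 − c))] = 0.049, 0.044 and 0.039.

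The unadjusted test gets part of that benefit anyway, because stratification has already reduced the true variance. With SE = √[(1.03² + 1.00²)/133], the normal approximation gives:

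- unadjusted, 1 − Φ[(1.960 × SE − 0.35)/(√(1 − c) × SE)]: 80.4%, 80.9%, 81.5%
- adjusted, 1 − Φ[1.960 − 0.35/(√(1 − c) × SE)]: 80.7%, 82.2%, 84.2%

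The net gain from naming centre is therefore about 0.3 to 2.7 points.

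**Step 5: QLQ-C30 and HAMD.** If change is compared, the ratio in step 3 applies. If week-6 scores are compared, as the wording of the Statistical analysis section allows, baseline is unused and the ratio is 1 − r²: 0.91, 0.75 and 0.51 for r = 0.3, 0.5 and 0.7.

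**The case against.** The strongest reply concerns the primary analysis. A general linear model accepts covariates, the article nowhere says that the model is unadjusted, and covariate lists are often left to an SAP that is not shown. This stands in part: for BFI-C one can say only that no term is named. It does not reach QLQ-C30 and HAMD, where the tests are named and cannot take covariates.

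A second reply is that the sample size rests on an unadjusted test, so the trial's size does not depend on adjustment. That is correct. The 133 per arm is not made wrong by this point.

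A reader might also infer more than the document supports:

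- **That the estimate is biased by regression to the mean from the entry threshold.** Both randomized arms meet the same threshold, so the effect cancels in expectation.
- **That any chance baseline imbalance passes in full into the result.** A change score already subtracts baseline. With equal SDs, a fraction 1 − r of the imbalance remains (0.7 to 0.3 for r = 0.3 to 0.7), in the opposite direction.
- **That a Wilcoxon test contradicts the promised mean difference and 95% CI.** The article says these are calculated as well, not that they come from the Wilcoxon test.
- **That every secondary score lacks a possible baseline adjustment.** CTRS has no described baseline, so only centre applies to it.
- **That adjustment is sure to make good the power lost to the dropout allowance.** With k below 1, several cells of the table stay under 80%.

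**Conclusion.** The point holds as one of efficiency. The analyses of QLQ-C30 and HAMD, as fixed, cannot use baseline or centre, and the BFI-C analysis names neither, although both are available. The consequences are lost precision and mildly conservative tests (type I error about 0.039 to 0.049 if centre explains 10% to 1% of variance). Neither bias nor an invalid test follows.

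The size of the loss is uncertain. At 128 completers per arm, baseline adjustment would take power from 78.5% to about 85 to 93% with equal SDs, but only to about 78.5 to 87% with a baseline SD of 0.6 to 0.8 of the week-6 SD. The centre effect is small throughout. All of this rests on assumed values of r, k and c. What does not depend on their exact values is the direction: apart from the few degrees of freedom spent, ANCOVA has no larger error variance than the change score. The change is worth making, but the trial remains interpretable without it.

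**What to change.** Amend the Statistical analysis section before unblinding:

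- **BFI-C:** analyse week-6 change with baseline BFI-C and centre as covariates, by ANCOVA or as the week-6 contrast of a mixed model.
- **Each QLQ-C30 scale and HAMD:** use the same form, with that scale's own baseline plus centre, and report the adjusted mean difference with its 95% CI.
- **CTRS:** adjust for centre only.
- **Wilcoxon rank-sum test:** keep it as a sensitivity check, not as an alternative main analysis.

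The cost is wording. No extra data or visits are needed. With four centres, the model spends 3 degrees of freedom on centre and 1 on baseline. The sample size need not change. If the sponsor wants to count on a power gain, r and the SD ratio should first be estimated from earlier data and stated.
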